### **9.3 Data Collection and Management**

Information will be transmitted and stored using state-of-the-art security systems similar to those that protect websites used by banks and electronic health record systems. Specifically, the Eureka Platform is hosted on Amazon Web Services (AWS), a cloud-based server system and computing services that are HIPAA compliant, and Eureka follows security guidelines of the U.S. Health Insurance Portability and Accountability Act of 1996 (HIPAA). Specifically, all research data are stored behind a secure firewall, guarded by intrusion detection software, and encrypted at rest and in transit in our Amazon Virtual Private Cloud. The network, including all the servers that will store our research data, is behind a secure firewall that does not allow unauthorized access to any research data server.

The Eureka Privacy Policy and Data Security Measures statement will inform participants of the risks of loss of privacy, including via technical compromise or legal requirements. We will also make participants aware that they are responsible for keeping their login credentials secure.

To minimize risk of loss of privacy, Mosio holds to the following policies, derived from Mosio's Privacy Policy: "Personal information is never shared outside Mosio without permission, except under conditions explained below. Inside Mosio, data is stored in security-controlled, HIPAA-compliant servers with limited access. Information may be stored and processed in the United States or any other country where Mosio, its subsidiaries, affiliates or agents are located.

Mosio may send personal information to other companies or people under any of the following circumstances:

- When they have consent to share the information
- If sharing information is necessary to provide a product or requested service (If information is shared with third parties we only provide the information they need to deliver the service. Also, such companies are prohibited from using information for any other purpose)
- To keep users up to date on the latest product announcements, software updates, special offers or other information we think users would like to hear about (unless users have opted out of these types of communications)
- If required to do so by law, to enforce the Terms of Use, or in urgent circumstances, to protect personal safety, the public or their websites

An audit trail will record all logins and any changes to study data, and all study data is housed on a secure server. All servers are protected from viruses using anti-virus software. This software automatically checks for virus signature file updates once an hour, and if necessary, directly updates itself. All antivirus software is monitored and network personnel notified in the event that the software stops functioning on a server.

The study database is backed up regularly to ensure that no data is lost. Our disaster recovery system also follows Standard Operating Procedures to maintain full security.

## 10.0 Statistical Methods

### 10.1 Sample Size and Randomization

The goal is to enroll at least 80 participants with full completion of all study measures. Recruitment of 80 patients will be both feasible in terms of budget and sufficient in size to detect differences in ectopy in response to caffeine. CHS data on PACs/hour and PVCs/hour were used in power calculations to determine the minimal detectable percentage increase (MDPI) in ectopy with 80% power. The MDPI with a sample size of 20 was 70%, compared to 30% with 80 subjects.

We will perform in-person recruitment, supported by [name], post-doctoral fellow, and [name] CRCs. Given the N-of-1 strategy, the effect of caffeine on a single patient can be combined in a multilevel statistical model to increase study power.

### 10.2 Statistical Analysis Plan (SAP) and Outcome Assessment

For our primary outcome, we will analyze differences in PAC and PVC counts on days participants were randomized to consume coffee vs. avoid coffee. As secondary outcomes, we will compare differences in SVT and VT episodes, mean daily glucose levels, mean step count, and mean sleep duration, also for days randomized to consume coffee vs. avoid coffee.

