#### 4.4 Randomization Scheme

128 unique combinations of A & B were generated, and each was assigned a number between 1-128.

Numbers 1-128 were randomized; the new order of number corresponds to the randomization scheme for each additional enrolled participant. I.e., the new order could be: 48, 19, 52, 102, 3, etc. This means participant #1 will receive randomization scheme 48, participant #2 will receive randomization scheme #19, and so on. If participants early terminate, the next participant will take up the next available number.

If/when all 128 numbers are exhausted, numbers 1-128 are re-randomized into a new order, and the next participant will take on the first available randomization.

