## 2.2 Study Objectives

The objectives of this trial are to study the real-time physiological consequences of caffeine consumption. We aim to specifically elucidate how caffeine affects glucose levels, sleep quality, physical activity, and daily ectopy on a day-to-day basis.

Primary objectives:

- To compare the changes in PACs and PVCs on days where participants were randomized to drink coffee vs. randomized to avoid caffeine
- To analyze the relationship between caffeine intake and general health measurements, ie. physical activity and sleep health

Secondary exploratory objectives include assessment of the following:

- To assess if physical activity, daily glucose levels, and sleep mediate coffee-ectopy relationships
- To assess if genetically-determine differences in caffeine metabolism influence the aforementioned associations

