During the study, patients will receive a text or push notification from the Eureka app or Mosio software each day with instructions for allowance or restriction of coffee intake the following day and will also receive daily queries regarding consumption that occurred the previous day. A cup of coffee will be defined as one 8 oz coffee (130-180mg caffeine, depending on roast), or two espresso shots (150-170mg caffeine). In order to avoid >2 consecutive days with or without coffee, participants will be randomized in pairs of either "off one day and on the next day" or "on one day and off the next day". All participants will be instructed to press the button on the ZIO® XT Patch whenever they have a cup of coffee. All patients will also receive a Fitbit Inspire to assess step counts and sleep. Patients will "opt in" to share their data with Eureka via an API (Application Programming Interface, see more details in Section 12.1). Participants will consent by clicking an "opt in" web form from the Eureka platform, and then complete the opt-in procedure specified and managed by each third party. Participants who do not download Eureka will consent to share their fitness tracker information with the study team through Health eHeart (CHR #12-09993) in Module 5. In addition, we will be monitoring how glucose levels fluctuate with changing caffeine habits, thus participants will also be given a continuous glucose monitor to wear for the duration of the study.

During the final visit, the study staff (i.e. study coordinator) will meet the study participant at UCSF (i.e. in the Clinical Research Center) at the time specified by the study participant. Next, the study staff will remove the external remote cardiac monitor (i.e. ZIO® XT Patch) and continuous glucose monitor (i.e. Dexcom G6). Upon participant request, study staff can provide individual-level results collected from the device and provide reports showing randomizations over the enrollment period (dates randomized to consume caffeine vs abstain from caffeine). The study staff will then collect back the fitness tracker (i.e. Fitbit INSPIRE device). Once all equipment has been returned, the study staff will assess the participant's study compliance and conduct quality checks for equipment data collection. At this time, the study staff will also reimburse the participant for all caffeine purchases upon proof with time-stamped receipts.

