## **5.2 Monitoring Period**

The monitoring period is Day 1-14. Participants will be receiving daily instructions at 08:00 and reminders at 20:00, as well as their daily surveys. The AM message includes instructions for the day, and daily surveys for caffeine use and sleep. The PM message includes instructions for the next day, and daily surveys for mood and headaches.

After Day 14, participants are welcome to resume their normal caffeine habits, and will be prompted to do so by the PM message. Participants will receive their final message on Day 15, to finish their last set of surveys and will be reminded to resume their normal caffeine habits.

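### Two of every participant's seven coffee/avoid pairs set a weekend day against a weekday, and section 10.2 names no weekend term for steps and sleep: a minor, free gain in precision

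*Supplement*

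**What the plan says.** - **Assignment.** Protocol section 3.0 (Study Treatment) states that "participants will be randomized in pairs of either" off-then-on or on-then-off, so that nobody has more than two like days in a row. Section 5.2: "The monitoring period is Day 1-14". The operations manual, section 4.4, gives the number of schedules: "128 unique combinations of A & B were generated, and each was assigned a number between 1-128". Day 1 is not tied to a day of the week.
- **Comparison.** For the primary outcome, section 10.2 (SAP and Outcome Assessment) says "we will analyze differences in PAC and PVC counts on days participants were randomized to consume coffee vs. avoid coffee". The secondary outcomes include step count and sleep duration, "also for days randomized to consume coffee vs. avoid coffee".
- **Model.** Section 10.1 says that individual effects can be combined in a multilevel model. Neither it nor the two parts of 10.2 lists any terms: no weekend, day-of-week, study-day or pair term.
- **Standing of steps and sleep.** Section 10.2 treats them as secondary outcomes, but section 2.2 lists this among the primary objectives: "To analyze the relationship between caffeine intake and general health measurements, ie. physical activity and sleep health". The power figures in 10.1 concern ectopy only.

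**The concern.** Pairing adjacent days is meant to set like against like. Seven is odd, so the pairing shifts by one weekday between the first and second week. One of the two weekends then cannot sit inside a single pair. Its Saturday is paired with a Friday and its Sunday with a Monday.

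If people walk or sleep differently at weekends, those two differences carry the weekend effect as well as the coffee effect. Its sign depends on which day drew coffee. Without a weekend term, this calendar variation is counted as noise. At stake is the width of the intervals for step count and sleep duration, not the validity of the comparison.

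**Working it through.** **Inputs.** Fourteen days (section 5.2); on/off pairs of consecutive days (section 3.0); 128 schedules (operations manual 4.4); 80 completers (section 10.1). The weekend effect d, in units of the within-person day-to-day SD s, is not in the documents. It is assumed to lie between 0.25 and 1.0.

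**1. The plan's own figure.** 14 / 2 = 7 pairs, each with two possible orders, gives 2⁷ = 128. This matches the manual and confirms seven independent binary pairs.

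**2. Mixed pairs, for every start day.**

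| Day 1 | Fri/Sat pair | Sun/Mon pair | Sat/Sun pair |
|---|---|---|---|
| Mon | Days 5-6 | Days 7-8 | Days 13-14 |
| Tue | Days 11-12 | Days 13-14 | Days 5-6 |
| Wed | Days 3-4 | Days 5-6 | Days 11-12 |
| Thu | Days 9-10 | Days 11-12 | Days 3-4 |
| Fri | Days 1-2 | Days 3-4 | Days 9-10 |
| Sat | Days 7-8 | Days 9-10 | Days 1-2 |
| Sun | Days 13-14 | Days 1-2 | Days 7-8 |

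Two of seven pairs are mixed in every row. The count is the same if the weekend is taken as Friday and Saturday nights, as one might for sleep.

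**3. Balance of weekend days.** The Sat/Sun pair always gives one weekend day to each condition. The other two weekend days are allocated independently. Of the 128 schedules, 64 split the four weekend days 2:2 between coffee and avoid, 32 split them 3:1 and 32 split them 1:3. The imbalance averages to zero, so there is no bias.

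**4. Variance.** A participant's coffee-avoid difference is the mean of seven pair differences. Each has variance 2s² from daily noise. The two mixed pairs each add +d or -d with equal chance, which is variance d² (d here on the outcome scale). Hence

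Var = (1/49)(7 × 2s² + 2d²) = (2/7)(s² + d²/7).

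With s = 1, the inflation is 1 + d²/7:

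| d | d²/7 (extra participants needed) | SE ratio √(1 + d²/7) | Power with the term, if 80% without it |
|---|---|---|---|
| 0.25 | 0.9% | 1.0045 | 80.4% |
| 0.5 | 3.6% | 1.018 | 81.4% |
| 1.0 | 14.3% | 1.069 | 85.0% |

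The power column assumes a two-sided 5% test, since the plan states no alpha. At d = 1.0 the loss corresponds to 80 / 7, or about 11 participants.

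**5. Simulation check.** 80 participants × 14 days, 1,500 replicates, random start weekdays, fixed coffee effect. Empirical SE without and with a weekend term:
- no weekend effect: 0.0592 and 0.0593
- d = 0.5: 0.0615 and 0.0606
- d = 1.0: 0.0634 and 0.0596

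The average error of the unadjusted estimate was within 0.003 of zero throughout. Without a weekend effect, the term costs essentially nothing.

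**The case against.** The case against has several parts, and much of it stands.

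- **The premise is external.** No section says that steps or sleep differ at weekends, or by how much. That stands. The effect is plausible, but its size is assumed, and at d = 0.25 the gain is negligible.
- **The gain is a ceiling.** If the coffee effect itself varies between participants with variance τ² (s = 1), the inflation falls to (2/49)d² / (τ² + 2/7), which is below d²/7. If weekend effects differ between people, a common term removes only their average. Both points stand.
- **This is one symptom of a model with no listed terms.** True. It is still a concrete item with an exact structural cause, and the calendar day is fixed before assignment and cannot be affected by it.

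A reader might also infer more than the documents support:

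- **That the coffee effect is biased.** It is not, because order within pairs is randomised.
- **That up to 20% more participants would be needed at d = 1.0.** That comes from the day-level residual variance: 4 of 14 days are weekend days, so (4/14)(10/14)d² = (10/49)d², or 0.204. This is what a day-level model without pairs would report as residual variance. The actual sampling variance follows the pair formula and gives 14%.
- **That individual N-of-1 results are confounded.** In the half of schedules split 3:1 or 1:3, a person's own difference does shift by (2/7)d, or 0.29 SD at d = 1.0, against an individual SE of √(2/7) = 0.53 SD. But section 10.2 plans no individual effect estimate for steps or sleep, and a common fixed term would not remove one person's own weekend effect.
- **That ectopy, SVT/VT or glucose are affected.** The argument is made only for steps and sleep.

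**Conclusion.** The point holds as a minor matter of efficiency. The count of two mixed pairs in seven is exact for any start day on the planned schedule, and no weekend term is named. The cost is a standard error for the step-count and sleep contrasts that is larger by roughly 0.4% to 6.9% over the assumed range of d. The contrast remains unbiased.

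The figures rest on four assumptions: d between 0.25 and 1.0 within-person SDs, complete 14-day data, a coffee effect common to all participants, and schedules that act as independent draws. Missing days or early termination would change the counts in the analysed data. The operations manual deals the 128 schedules without replacement, which would make the penalty smaller if start days cluster on particular weekdays.

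**What to change.** In section 10.2 (SAP and Outcome Assessment), prespecify a fixed weekend indicator, or day of week, in the multilevel models for step count and sleep duration. For sleep, state which nights count as weekend. Keep the unadjusted coffee-avoid contrast as a sensitivity analysis. Using the term in the other outcome models is optional.

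The cost is one line in the plan and one degree of freedom for an indicator (six for day of week), out of about 80 × 14 = 1,120 participant-days. The dates are already known, so no data collection is added. Fixing the term in advance also removes a later choice of covariate.

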#### 10.2 Intention-to-Treat (ITT)

The main intention-to-treat (ITT) analysis set will include all randomized participants, whether or not they are compliant with the treatment allocation for this trial. Every attempt will be made to collect data until the end of the follow-up period for all randomized participants and these data will be included as part of the main ITT analysis. The analyses for the primary objective will be performed using the ITT dataset.

As-treated analyses utilizing counts of coffee consumed inferred by the patient activation button on the Zio patch will be employed to assess quantitative relationships.

Although substantial crossover is not anticipated, per protocol analyses will also be conducted if failure to comply with allocated treatment assignments occurs in more than 10% of cases or if there is a significantly different proportion of assignment adherence in one group compared to the other.

## 11.0 Ethical Considerations

This study is to be conducted according to US and international standards of Good Clinical Practice (FDA Title 21 part 812 and International Conference on Harmonization guidelines), applicable government regulations and Institutional research policies and procedures.

### 11.1 Institutional Review Board (IRB) and Ethics Committee (EC) Approval

This protocol and any amendments will be submitted to a properly constituted independent IRB for each clinical site, in agreement with local legal prescriptions, for formal approval of the study conduct. The decision of the IRB concerning the conduct of the study will be made in writing to the Principal Investigator and a copy of this decision will be provided to the funder before commencement of this study. The Principal Investigator should also provide a list of IRB members and their affiliate to the UCSF CC.

### 11.2 Informed Consent

The investigator must explain to each participant the nature of the study, its purpose, the procedures involved, the expected duration, the potential risks and benefits involved and any discomfort it may entail. Each participant must be informed that participation in the study is voluntary and that he/she may withdraw from the study at any time and that withdrawal of consent will not affect his/her subsequent medical treatment or relationship with the treating physician.

This informed consent should be given by means of a standard written statement, written in non-technical language. The subject should read and consider the statement before signing and dating it, and should be given a copy of the signed document. If the participant cannot read or sign the document, oral presentation may be made or signature given by the participant's legally appointed representative, if witnessed by a person not involved in the study, mentioning that the participant could not read or sign the documents. No participant can enter the study before his/her informed consent has been obtained.

The informed consent form must be submitted by the investigator for IRB approval. An informed consent template will be provided to all of the clinical sites for their use.

### 11.3 Declaration of Helsinki

The investigator must conduct the trial in accordance with the Declaration of Helsinki.

## 12.0 Protocol Amendments

Any change or addition to this study protocol, which significantly affects the safety of participants, the scope of the investigation or the scientific quality of the study, will require a

written protocol amendment. The site must receive IRB approval for the amendment, prior to implementation.

### **Summary of Protocol Changes**

As an investigator-initiated study (not designed as part of a formal product investigation, such as for the Food and Drug Administration), the initial protocol was drafted as an operations manual. Subsequently, but prior to the final analyses and drafting of the manuscript, a protocol that more completely incorporated details included in the approved Institutional Review Board application and ClinicalTrials.gov was completed. Therefore, while the content of the written document changed, the study design itself did not.
